# Energy and protein intake in medical and geriatric inpatients with MEDPass versus conventional administration of oral nutritional supplements: study protocol for the randomized controlled MEDPass Trial

**DOI:** 10.1186/s13063-021-05145-4

**Published:** 2021-03-16

**Keywords:** Oral nutritional supplements, Energy intake, Protein intake, Malnutrition, MEDPass, Nutrition as medication, Medication rounds

## Abstract

**Background:**

Disease-related malnutrition is highly prevalent in hospitalized medical and geriatric inpatients. It is associated with negative outcomes such as muscle wasting, decline of functional status, and increased morbidity and mortality. Oral nutritional supplements (ONS) are frequently used in nutritional therapy to increase intake. However, compliance to ONS is often limited and maybe improved by prescribing ONS in small portions timed with the medication (MEDPass). However, it is unknown whether the MEDPass administration enhances patients’ total energy and protein intake.

**Methods:**

The MEDPass Trial is a randomized, controlled, open-label superiority trial. Patients in the MEDPass group receive 50 ml of ONS four times per day, distributed with the medication rounds. Patients in the control group receive ONS between meals. The primary outcome is average daily energy intake (% of calculated daily requirement). For our power analysis, we assumed that administration of ONS in the MEDPass administration mode increases energy intake by at least 10% (i.e., by 200 kcal for an average energy requirement of 2200 kcal/day). Thus, with the inclusion of 200 patients, this trial has 80% power to demonstrate that intervention group patients have an average intake of 2200 kcal/day (SD 500 kcal) versus 2000 kcal/day (SD 500 kcal) in control group patients. Energy and protein intakes from ONS and all food consumed are monitored continuously throughout the hospital stay and are statistically compared to the patient’s requirements. Secondary outcomes include average daily protein intake (% of calculated daily requirement), average intake of ONS/day, the course of body weight, handgrip strength, appetite, and nausea. Furthermore, hospital length of stay and 30-day mortality are assessed. The primary statistical analysis will be performed as an intention-to-treat analysis adjusted for the stratification factors used in randomization.

**Discussion:**

To our knowledge, this is the first randomized controlled trial assessing total energy and protein intake for the entire hospitalization period in patients receiving MEDPass versus conventional ONS administration. Thus, the MEDPass Trial will fill a gap and answer this relevant clinical question.

**Trial registration:**

ClinicalTrials.gov NCT03761680. Registered on 3 December 2018. Kofam.ch SNCTP000003191. Registered on 15 October 2018

## Background

Disease-related malnutrition (DRM) in hospitalized patients is a common problem with an estimated prevalence of 20–60% [1–3]. DRM is associated with detrimental clinical and metabolic consequences, such as catabolism, muscle wasting, impaired muscle function, and mobility [4, 5]. DRM is also associated with higher mortality and morbidity rates and increased hospital length of stay (LOS) [3, 4, 6]. These outcomes not only affect quality of care, but also pose a substantial economic burden [3].

In inpatients at nutritional risk, an adequate and early nutritional therapy has been shown to be effective, significantly reducing severe complications and 30-day mortality [6, 7]. Oral nutritional supplements (ONS) are one of the most common treatments for DRM, and ONS are designed for this specific medical purpose [8, 9]. The use of ONS has proven efficient and cost-effective [10, 11]. Treatment with ONS may reduce mortality and complications, attenuate or prevent muscle loss, and improve nutritional status and function [10, 12, 13]. The European Society of Clinical Nutrition and Metabolism (ESPEN) recommends the use of ONS for medical and geriatric patients at nutritional risk [10, 14]. These patients often live with chronic illness, which is associated with appetite and body weight loss. Thus, the risk of DRM is increased [10].

Compliance with ONS is often described as suboptimal. This poses a barrier to adequate oral nutrition therapy [14, 15]. The ONS administration mode may be one of the keys to improving compliance. There are no standards on how to administer ONS in terms of timing and dose throughout the day, which leads to individual approaches. In the hospital setting, ONS are conventionally served by nurses, nursing aids, or catering personnel between main meals. The MEDPass administration mode offers a different approach, in which ONS are distributed on medication rounds three or four times per day in unusually small portions (50–120 ml) [16–22]. Preliminary trials suggest that the MEDPass administration mode improves compliance and cost effectiveness [17, 19, 22, 23].

However, since ONS are dense in energy and protein, they may have a negative impact on appetite [24]. Consequently, enhancing compliance with ONS may not automatically lead to improved nutritional intake throughout the day because conventional food intake may decline. Therefore, this trial will study total energy and protein intake throughout the day as primary outcome measures when ONS are administered in the MEDPass mode versus the conventional administration mode. To our knowledge, there has never been a prospective trial in which total energy and protein intake was studied consistently and systematically. Therefore, the aim of this trial is to fill this clinically relevant gap of knowledge.

## Methods

### Study design

The MEDPass Trial is a randomized, controlled, clinical trial (RCT) conducted with parallel groups. Blinding of patients is not possible because of the evident differences in ONS administration times. Therefore, it is conducted as an open-label RCT. The MEDPass Trial is a superiority trial. The allocation ratio of intervention group and control group is 1:1.

### Study population

The MEDPass Trial includes medical as well as geriatric inpatients at the Tiefenau facility of the University Hospital of Bern. It includes inpatients of the Department of Geriatrics and the Department of General Internal Medicine who meet the eligibility criteria listed in Table 1.

**Table 1 Tab1:** Inclusion and exclusion criteria

**Inclusion criteria**	• Nutritional Risk Screening (NRS 2002) total score ≥ 3 points according to routine screening at admission within 72 h [25] • Expected hospital LOS ≥ 3 days after screening (as estimated by the treating physician) • Patient qualifies for ONS and approves prescription • Age > 18 years • Willingness and ability to provide informed consent
**Exclusion criteria**	• Initially admitted to critical care unit • Immediate post-operative phase (< 7 days post-surgery) • Dysphagia with the inability to swallow liquids • Admitted with or scheduled for supplemental or total enteral nutrition and/or parenteral nutrition • Mini Mental State examination < 16 points • Hospitalization due to anorexia nervosa, acute pancreatitis, or acute liver failure • Patients with cystic fibrosis, short bowel syndrome, or after gastric bypass surgery • Terminal condition (end of life situation) • Poor German language skills (study language)

### Study intervention and comparator

Every patient in the MEDPass group receives 50 ml of ONS four times per day distributed by the registered nurses (RN) on the ward during medication rounds. Three out of the four medication rounds occur approximately 30 min before the main meals’ distribution, and the evening medication round is at 10 pm. Patients are counseled to take the ONS directly at the start of the meal to avoid any possible interaction with medications. The control group regimen was chosen to compare the MEDPass administration mode to usual clinical practice. Usual practice of ONS administration at the study site is unstandardized. This kind of prescription may range from one up to four bottles of ONS per day and is served between the meals or after the evening meal. Patients in the control group receive ONS between meals according to unstandardized prescriptions. The staff was instructed not to make any changes to the procedures followed before the initiation of the trial. This means that the amount of ONS prescribed to control group patients might be higher than those of the intervention group. However, compliance with ONS may be better with the MEDPass-mode. Compliance in the context of the MEDPass Trial is defined as the percentage of prescribed ONS consumed. Furthermore, patients receiving ONS in the MEDPass administration mode may be able to eat more additional food between meals than those receiving ONS between meals. Thus, we hypothesize that MEDPass group patients are more likely to reach their energy and protein targets even if their net prescription of ONS is lower.

### Type of ONS used in the MEDPass trial

All ONS used in this trial are selected according to patients’ nutritional needs and flavor preferences. Patients may choose from a wide range of available products at University Hospital of Bern. All products with an energy density of 1.5 kcal/ml and 2 kcal/ml are included in this trial. Overall, eight different ONS with this energy density are in stock. The amount of protein in these ONS ranges from 4 to 10 g/100 ml. Six of the ONS are nutritionally complete. Two of them do not contain any fat. The ONS are from different providers (Abbott Nutrition, Fresenius Kabi, Nestlé Health Science). If patients require an ONS that is not available in the standard assortment of the University Hospital, it can be ordered if it is obtainable on the Swiss market.

### Ethical aspects

The study is carried out in accordance with the current version of the World Medical Association Declaration of Helsinki protocol [26], ICH-GCP guidelines [27, 28] or ISO 14155 norm [29] and according to the Swiss Federal Act on Research involving Human Beings [30, 31].

### Randomization

Randomization is stratified according to the NRS 2002 total score and the energy content of the ONS (kcal/ml). The NRS 2002 total score is stratified as NRS 3, NRS 4, or NRS 5-7. The energy content of the ONS is stratified as either 1.5 kcal/ml or 2 kcal/ml. Even distribution of these factors between the groups minimizes bias since they may directly influence primary and secondary outcome parameters. Randomization is conducted using the Research Electronic Data Capture (REDCap®) program (Vanderbilt University, Nashville, TN, USA, 2020, version 9.1.15). Registered Dietitians (RD) input the stratification data and randomize electronically within the REDCap® program. The RDs do not have access to the concealed randomization sequence. The randomization list with random numbers for coding was pre-specified by the Clinical Trial Unit (CTU) Bern and electronically integrated into the REDCap® database.

### Outcomes

The primary outcome is the average energy intake/day (kcal, % of calculated daily requirement). Secondary outcomes include average protein intake/day (g, % of calculated daily requirement), average ONS intake/day (ml), the course of handgrip strength (kg), body weight (kg), appetite, and nausea. Furthermore, hospital LOS and 30-day mortality are assessed.

### Study conduct and data collection

Participants are recruited consecutively. Based on routine screening upon admission, patients with an NRS 2002 total score of > 3 are referred to the RDs [25, 32]. The RDs check the eligibility criteria. If there is an indication but no ONS prescribed, the RDs counsel the patient concerning ONS. Once an eligible patient agrees to a prescription of ONS and an appropriate product is selected, the patient is informed by the RD about the possibility of participating in the trial. Upon approval, the RD obtains informed consent and randomizes the patient. The prescription of ONS is carried out by the medical doctors (MD). All involved personnel (MDs, nursing and catering staff) is informed by the RDs of the patient’s participation in the trial. An overview of the patients’ flow is given in Fig. 1 and an overview of the time schedule for participants is provided in Table 2. The trial is only concerned with ONS administration and has no influence on any other aspects of patients’ treatments. ONS may be discontinued if the indication therefore no longer exists.

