#### Sample size calculation

Based on our clinical experience, we assumed for our power analysis that administration of ONS in the MEDPass mode increases energy intake (primary endpoint) by at least 10% (i.e., by 200 kcal from an average of 2000 kcal/day). Furthermore, we assumed that an average patient weighs 75 kg and therefore has an approximate energy requirement of 2200 kcal. A final assumption is that in current clinical practice they may only receive 2000 kcal/day. Therefore, to demonstrate that intervention group patients have an increased average daily energy intake of 200 kcal/day (i.e., from 2000 (SD 500 kcal) to 2200 (SD500 kcal)), we need to include 200 patients to achieve 80% power (alpha error of 0.05). The power calculation used the sampsi command in STATA® (Stata Corp, USA, 2017, version 15.3). Importantly, this trial is not powered to investigate whether the difference in energy intake of 200 kcal/day makes a significant difference to clinical outcomes. However, a similar increase in energy intake has previously shown to decrease the risk of adverse outcome and mortality [7].

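### The referral threshold (NRS 2002 above 3) contradicts the eligibility threshold (3 or more) and, read literally, does not reach the NRS 3 randomisation stratum

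*Protocol article*

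**What the plan says.** Three places in the Protocol article set or imply an NRS 2002 threshold for entry.

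- **Study population, Table 1.** The inclusion criterion is "Nutritional Risk Screening (NRS 2002) total score ≥ 3 points according to routine screening at admission within 72 h".
- **Randomization.** "The NRS 2002 total score is stratified as NRS 3, NRS 4, or NRS 5-7". The second factor has two levels: "The energy content of the ONS is stratified as either 1.5 kcal/ml or 2 kcal/ml".
- **Study conduct and data collection.** After routine screening at admission, "patients with an NRS 2002 total score of > 3 are referred to the RDs". The steps that follow belong to the dietitians: "The RDs check the eligibility criteria", and later "Upon approval, the RD obtains informed consent and randomizes the patient". The same section describes recruitment as consecutive.

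The Discussion adds context. It mentions medical patients who drop out of consideration after screening and referral because their remaining stay is too short. It also says, in retrospect, that having the dietitians do the nutritional screening might have been more efficient. So other staff did the screening, and the dietitians depended on referral.

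**The concern.** The referral sentence is an operative rule. It describes how a screened patient reaches the person who applies the eligibility criteria and randomises, and its threshold is stricter than the eligibility threshold. The score takes whole-number values, so the two rules differ at exactly one value, 3, and that value is a complete randomisation stratum.

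What is at stake is who the trial represents. The Discussion rests the trial's value on a deliberately broad population at nutritional risk. If wards followed the referral sentence literally, patients at the lowest eligible score would not be approached by the described route. The results would then apply to a narrower group than Table 1 defines. A reader of the article cannot tell which threshold was used.

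**Working it through.** **Step 1. The plan's own figure.** The Sample size calculation section gives 200 patients for 80% power, means of 2000 and 2200 kcal/day, SD 500 and alpha 0.05. The test is assumed two-sided, since sidedness is not stated. Allocation is 1:1 (Study design).

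- Per arm: n = 2 × (1.960 + 0.842)² × (500/200)² = 2 × 7.85 × 6.25 ≈ 98.1, rounded up to 99. The total is 198, which agrees with the stated 200.
- Power at 100 per arm: 200 / (500 × √(2/100)) − 1.960 = 2.828 − 1.960 = 0.868, which gives 80.7% (80.4% with the t distribution).

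No input to this calculation involves the NRS score, so the threshold question leaves it unchanged.

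**Step 2. The thresholds as sets of scores.** The strata run up to 7.

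| Rule | Section | Scores admitted |
|---|---|---|
| Eligibility | Study population, Table 1 | 3, 4, 5, 6, 7 |
| Strata | Randomization | {3}, {4}, {5, 6, 7} |
| Referral | Study conduct and data collection | 4, 5, 6, 7 |

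Eligible but not referred: {3, 4, 5, 6, 7} minus {4, 5, 6, 7} = {3}.

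**Step 3. The strata.** There are 3 NRS levels × 2 energy densities = 6 cells. Scores admitted by both rules number 0 in level 3, 1 in level 4 and 3 in level 5-7. The cells with no admitted score are NRS 3 at 1.5 kcal/ml and NRS 3 at 2 kcal/ml, which is 2 of 6. With a referral threshold equal to the Table 1 threshold, all 6 cells can be filled.

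**Step 4. Whether another route exists.** In the article, eligibility checking, patient information, consent and randomisation all follow referral. No second route to the dietitians is described. Figure 1, the patient flow, is not available here and might show one.

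**Step 5. What cannot be computed.** The number of patients missed would be the screened pool multiplied by the share scoring exactly 3. The article gives neither. It does give recruitment status: 126 recruited by 8 September 2020, so 200 − 126 = 74 remained. That is the number for whom a correction could still matter at that date, not an estimate of loss.

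**The case against.** The strongest reply is that this is a slip of one character in a narrative sentence. Table 1 and the strata agree with each other, and the randomisation list was prepared by the trial unit and built into the database. The article is also loose with inequality signs elsewhere: Table 3 uses only strict signs for age 65 and BMI 18.5, so neither boundary value is covered. The referral sentence does not say that only patients above 3 are referred, and the dietitians then apply the Table 1 criteria. Screening forms, training material and the full protocol may all carry the threshold of 3.

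Much of this stands. A slip is the likeliest explanation, and nothing in the article shows that the NRS 3 stratum was in fact left empty. The reply does not remove the contradiction, though. The sentence sits in the Methods and states an entry threshold. Dietitians can apply Table 1 only to patients who reach them, and the article describes no other way for a patient scoring 3 to do so.

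A reader might also infer larger consequences, which the document does not support:

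- **Bias between arms.** Referral precedes randomisation, so it cannot differ by allocated arm.
- **A broken adjusted analysis.** An empty level of a stratification factor simply drops out of the regression; the model remains valid.
- **A cause of slow recruitment.** The Discussion attributes the delay mainly to organisational barriers, and also cites short medical stays and difficulty with consent. It mentions no screening threshold.
- **A sicker population.** NRS 2002 measures nutritional risk. The most that follows is that the lowest eligible risk score would be missing.

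**Conclusion.** The concern holds as an internal contradiction about who can enter the trial. Taken literally, the referral rule does not reach one eligible score, which is one of three NRS levels and 2 of 6 randomisation cells. The enrolled population would then be narrower than Table 1 states, and recruitment would not be consecutive with respect to that population.

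This rests on two assumptions: that the sentence is applied as written, and that referral is the only route to the dietitians, as the article's text implies. Neither can be confirmed from the article. The validity of the randomised comparison and the sample size of 200 are not in question. The point calls for a correction and a check of conduct, and is no reason to doubt the design.

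**What to change.** 1. Change the referral sentence under Study conduct and data collection so that it agrees with Table 1 and the strata (a total score of 3 or more). This is a change of one character.
2. Confirm which threshold appears on the ward screening form and in the staff training material. The article says training is repeated because of staff turnover, so an error there would persist.
3. Tabulate enrolment by NRS class (3, 4, 5-7). The score is already recorded at baseline and entered for randomisation, so this needs no new data. A well-filled NRS 3 class would indicate that the problem is one of wording.
4. If the stricter threshold was used in practice, correct it for the remaining recruitment, report the period it covered, and describe the enrolled population accordingly.

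The cost is a text correction, a short document check and one table. The randomisation list, the sample size and the analysis model need no change.

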**Fig. 1 Fig1:**
[figure not shown]
Patients’ flow. NRS 2002, Nutritional Risk Screening 2002; ONS, oral nutritional supplement; RD, registered dietitian; SAE, serious adverse event

**Table 2 Tab2:** Time schedule for participants

Study period	Screening	Intervention period					Evaluation	Follow-up
Visit	1	2	3	4	5	6		
Day	0	1	8	15	22	29	*	**
NRS 2002 total score	x							
NRS 2002 subscore nutritional status	x							
Inclusion and exclusion criteria	x							
Information, informed consent	x							
Assignment to study group		x						
Baseline patient characteristics		x						
Energy intake/day (kcal)**		Continuous assessment						
Protein intake/day (g)**								
ONS intake/day (ml)**								
Serious adverse events (SAE)**								
Handgrip strength (kg)		x	x***	x***	x***	x***		
Body weight (kg)		x	x***	x***	x***	x***		
Body height (cm)		x						
BMI (kg/m^2^)		x						
Appetite (VAS)		x	x***	x***	x***	x***		
Nausea (VAS)		x	x***	x***	x***	x***		
Procedural variables							x	
Hospital LOS (d)							x	
30-day mortality (y/n)								x

*After patient dismissal or after 30 days of inclusion

**For 30 days upon inclusion

***Assessment at day 1, day 8, day 15, day 22, and day 29

Visits 2–6: study visits may be conducted earlier or later by a maximum of 2 days

The criteria for ONS discontinuation are:
ONS is not indicated anymore due to increased food intakeOccurrence of a serious adverse event (SAE) that necessitates a halt to the prescription

The reasons for discontinuation are documented. Furthermore, withdrawal from the trial is possible at any time at the patients’ request.

All data is inputted manually by the RDs into REDCap. REDCap is a program that provides the highest standard of data protection and an internal back-up system is in place to prevent data loss. The REDCap study database with all archive tables will be securely stored by CTU Bern for at least 15 years. The sponsor also keeps the Trial Master File (TMF) and interim/final reports for at least 10 years. All extracted data files are exclusively stored on password-protected personal computers. Source data is collected mostly from the electronic health record (EHR). This includes the NRS 2002, in- and exclusion criteria, patient characteristics, ONS intake, body weight, LOS, and safety outcomes. Meal cards, forms for collecting data on food intake between the meals and protein and energy intake calculations, are printed out and input manually into REDCap by the RDs. All trial-related paper documents are locked in a specific cabinet in the RD’s office during the whole study period. Afterwards, this material will be stored safely for 10 years in the locked archive of the Department of Endocrinology, Diabetes, Nutritional Medicine, and Metabolism at Bern University Hospital.

All participating staff have received formal training for all their tasks, and training materials are available on site on the intranet platform. Furthermore, training is provided continuously due to staff turnover. Regular exchange with appointed members of nursing and medical staff is implemented to monitor adherence to the protocol. The MEDPass Trial is managed and overseen by the study steering committee, the dietetic committee, and the data management committee. The study steering committee (authors SK, ER, PS, AWS, ABS, and ZS) is responsible throughout for main decisions on conduct including risk management, reports to the Competent Ethics Committee (CEC), and results dissemination. The study steering committee may bring forward suggestions for protocol amendments. If approved by the committee, they will be reported to the CEC. Substantial amendments are only implemented after CEC approval.

Under emergency circumstances, deviations from the protocol to protect the rights, safety, and wellbeing of human subjects may proceed without prior approval of the sponsor, the study steering committee, and the CEC. Such deviations shall be documented and reported to the sponsor, the steering committee, and the CEC as soon as possible.

All non-substantial amendments are communicated to the CEC within the Annual Safety Report (ASR). The trial registries will be updated within 30 days. Trial participants will be contacted via written communication and will be given the possibility to withdraw their approval.

The dietetic committee (authors SK, ABS and the team of RDs on site) oversee the implementation of recruitment, data collection, and the ongoing training sessions. The data management committee (authors SK, ER, MV, PS, AWS, and ZS) monitor data quality and are responsible for the statistical plan. During the recruitment period, an independent employee from Bern University of Applied Sciences will act as monitor, conducting at least one monitoring visit of the trial on site. The frequency and duration of the visits are dependent on the rate of subject enrollment, the quality of the study documents and the findings. During the visit(s), the monitor will check whether the trial is being carried out according to the study protocol and whether the subjects’ safety and rights are being protected. Furthermore, the monitor will review the collected trial data and verify source documents. The sponsor and the principal investigator on site allow the monitor direct access to all relevant documents during visits. They also agree to allocate their time and the time of their staff to the monitor to discuss findings and any other relevant issues.

In case of discrepancies, the monitor will make recommendations and schedule visits at shorter intervals. For each contact, a report is completed and signed by the monitor and the sponsor.

As category A trials are exempt from providing insurance, there is no specific insurance policy in place. However, general liability insurance is provided by Inselspital, Bern University Hospital.

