### Measurements

#### Energy, protein, and ONS intake

All parameters are assessed continuously until discharge or for a maximum of 30 days (Table 2). The RDs calculate daily energy and protein requirements according to relevant current clinical nutrition guidelines that apply to the patients in the MEDPass Trial [10, 14, 33]. The formula per patient is chosen according to age and body mass index (BMI). As some patients may suffer from progressive renal failure, the Clinical Practice Guideline of the National Kidney Foundation is used to calculate these patients’ protein needs [34]. The formulas for daily energy requirements as related to the primary outcome are listed in Table 3.

**Table 3 Tab3:** Calculation of daily energy requirements

Formulas for daily energy requirements		
	BMI < 18.5 kg/m^2^	BMI > 18.5 kg/m^2^
< 65 years	Actual body weight × 30 kcal [10]	Actual body weight × 27 kcal [10]
> 65 years	Actual body weight × 32 kcal [14]	Actual body weight × 30 kcal [14, 33]

Recommended protein intake is calculated according to the guidelines for geriatric and medical patients using the formula 1 g/kg body weight/day [10, 14, 33]. However, patients with chronic kidney disease and estimated glomerular filtration rate (eGFR) < 30 mL/min/1.73m^2^, who are not on dialysis, are an exception. In this case, the actual body weight is multiplied by 0.8 g/kg body weight/day [34].

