#### Hospital LOS and 30-day mortality

One of the co-investigators evaluates hospital LOS and 30-day mortality after the participants are released from the hospital or after 30 days of trial inclusion respectively (Table 2). Hospital LOS is assessed from the EHR as number of days: the calculation excludes the day of hospital discharge [36]. Hospital LOS is only assessed in medical inpatients since the geriatric inpatients have a prefixed duration of stay. Assessment of 30-day mortality is done by phone call to the patients’ home or the institution where the patient was referred to. If the patient is still hospitalized, the information is available in the EHR.

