#### Primary analysis

The baseline patient characteristics will be summarized for both groups. The primary analysis will be performed as an intention-to-treat (ITT) analysis including all randomized patients regardless of protocol adherence. In a further step, we will also do a per-protocol analysis excluding patients with major protocol violations as outlined below.

For the primary outcome, we will test whether MEDPass administration is superior to usual care and compare the average amount of daily energy intake using a Student’s *t* test or chi-square test. We will also fit linear regression models adjusted for initial NRS 2002 score and average amount of energy in the ONS, reported adjusted differences (coefficients), and corresponding 95% confidence intervals (CIs). Total energy, protein, and ONS intake throughout the study period will be divided by days of assessment per patient. Linear regression analysis adjusted for stratification factors will also be used for the evaluation of average daily protein intake as compared to the individual requirement (%) throughout the hospitalization, average intake of ONS/day (ml) throughout the hospitalization, and hospital LOS (days) between the groups. Logistic regression analysis adjusted for stratification factors will be is used for difference in 30-day mortality (yes/no) between the groups. Repeated measure models will be used for the evaluation of differences in course of handgrip strength throughout the hospitalization, weight changes throughout the hospitalization, and course of appetite and nausea throughout the hospitalization. The procedural variables will be analyzed and presented descriptively. There will not be a statistical safety assessment since there are no safety endpoints in the MEDPass Trial. Safety events will be presented descriptively.

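### Table 2 sets a 30-day window for serious adverse events, but the article describes no source for non-fatal events after discharge and other sections leave the end of collection unclear

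*Protocol article*

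**What the plan says.** Four parts of the Protocol article bear on when and how SAEs are collected.

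- **Table 2.** The SAE row carries the double-asterisk footnote, which reads "For 30 days upon inclusion". The rows for energy, protein and ONS intake carry the same mark. It is also the day entry of the Follow-up column, in which only 30-day mortality is ticked.
- **Study conduct and data collection.** "Source data is collected mostly from the electronic health record (EHR"). The items then listed as coming from it include "patient characteristics, ONS intake, body weight, LOS, and safety outcomes".
- **Measurements.** Under the heading on energy, protein and ONS intake: "All parameters are assessed continuously until discharge or for a maximum of 30 days (Table 2"). Under the heading on hospital LOS and 30-day mortality: "Assessment of 30-day mortality is done by phone call" to the patient's home or institution, with the EHR used for those still in hospital. The Safety outcomes section says that SAEs are followed continuously. It names aspiration pneumonia from ONS, and death linked to such pneumonia, as the potential SAEs. It gives neither an end date nor a method for the time after discharge.
- **Primary analysis.** No statistical safety assessment is planned. "Safety events will be presented descriptively".

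**The concern.** Read literally, the footnote opens a 30-day SAE window for every patient, while the source named for safety data is one hospital's record. A patient who goes home on day 5 and is treated for pneumonia on day 7 by another provider falls inside that window, yet no described step would find the event. A death in the same period would be found by the call, but the call is described as establishing whether the patient died, not why. Such a death could enter the mortality count without being classifiable as the pneumonia-related death that the Safety outcomes section names.

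If SAEs are seen only in hospital, each patient's observed time equals the stay after inclusion. Length of stay is itself a secondary outcome, so observed time could differ between arms. Safety is only described, so readers will compare raw counts, and those counts need a stated window and a denominator.

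**Working it through.** The plan gives no SAE rate, no SAE count and no distribution of stay, so it has no figure of its own to reproduce on this point. Its one computed figure, 200 patients, does reproduce (99 per arm by the normal formula, 100 per arm by the t-test version) but plays no part here.

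**Step 1: what the footnote means for SAEs.** Two readings are possible.

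- *Day 30 for everyone.* The wording has no discharge limit. The single-asterisk footnote beside it does mention discharge, so the authors wrote that limit in where they wanted it. The double asterisk also heads the Follow-up column, where mortality is followed beyond discharge.
- *Discharge, at most 30 days.* The same mark covers the intake rows, and the Measurements section, citing Table 2, ends those at discharge or day 30. The SAE row is grouped with these continuous assessments, and the Follow-up column is not ticked for SAEs.

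The discharge limit in Measurements stands under the intake heading and is repeated for handgrip strength, but not under Safety outcomes. The text does not settle which reading applies.

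**Step 2: which source covers which period.**

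| Period | Source described for SAEs | Source described for death |
|---|---|---|
| Inclusion to discharge | Hospital EHR | Hospital EHR |
| Discharge to day 30, readmitted to the same hospital | EHR, possibly | Call, or EHR if in hospital at day 30 |
| Discharge to day 30, treated elsewhere | None | Call; no step for cause |

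**Step 3: how much of a 30-day window would be observed.** The eligibility criteria require an expected stay of at least 3 days after screening; the other stays are assumptions. Observed share = days in hospital after inclusion / 30.

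- 3 days: 3/30 = 10%
- 7 days: 7/30 = 23%
- 10 days: 10/30 = 33%
- 14 days: 14/30 = 47%
- 21 days: 21/30 = 70%

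**Step 4: what a difference in stay would do, as an illustration only.** Assume a 30-day SAE risk of 10%, the same constant hazard in both arms, and stays of 10 and 12 days.

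- Daily hazard h = −ln(0.90)/30 = 0.00351
- Observed risk at 10 days: 1 − exp(−10h) = 3.5%
- Observed risk at 12 days: 1 − exp(−12h) = 4.1%
- Ratio: 0.0413/0.0345 = 1.20, with no true difference in hazard

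The documents support neither the 10% risk nor the 2-day difference. The calculation shows the mechanism, not an expected bias.

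**The case against.** The strongest reply is that there is no conflict. Hospital food intake cannot be measured after discharge, so for the intake rows the footnote must be a cap, and the SAE row carries the same mark. On that reading SAEs are collected in hospital for up to 30 days, which fits the EHR source. This is a fair reading, and it rules out calling the footnote a firm promise of 30-day follow-up. It does not remove the ambiguity: the footnote lacks the limit, and the Safety outcomes section does not supply it.

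Second, the article condenses a full protocol that is not shown, and that protocol may describe SAE reporting after discharge. This stands as a caution. The point therefore rests on what the article states about window, source and contact, not on silence alone.

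Third, a reader might infer that all events after discharge are missed. The text does not go that far: source data come mostly, not only, from the EHR; readmissions to the same hospital could be seen; and deaths are found by the call. A reader might also infer that the counts will be published as 30-day counts, or that the comparison between arms will be biased. The article says neither. Geriatric stays have a prefixed duration, so variable observation mainly concerns medical patients. The named SAEs are tied to ONS intake, and the trial gives ONS on the ward, so much of the relevant exposure falls in the observed period. A pneumonia that shows itself late remains possible, but the documents do not allow its frequency to be estimated.

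**Conclusion.** The concern holds as an inconsistency between window and source, not as proof of lost events. Table 2 states 30 days from inclusion; the only source named for safety data is the hospital record; the one contact described after discharge concerns death. The sections conflict or are ambiguous on when SAE collection ends. As described, non-fatal SAEs arising after discharge and treated elsewhere have no stated source, the cause of a death after discharge is not established, and observed SAE time follows length of stay.

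The effect on SAE counts cannot be derived from the documents. The 23% to 47% of the window observed rests on assumed stays of 7 to 14 days and on SAEs being seen only in hospital. The ratio of 1.20 needs an assumed difference in stay between arms as well. The primary outcome, its analysis and the sample size do not change. This is a low-cost improvement to the safety reporting, at the lower end of what should be changed.

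**What to change.** 1. Reconcile Table 2, the statement on EHR sources, the intake paragraph under Measurements, and Safety outcomes, so that all say whether SAE collection ends at discharge or at day 30.
2. If day 30 is meant, use the call already made for mortality to ask about pneumonia and hospital admission since discharge and, where a death is reported, its cause. Assess and record positive answers as SAEs.
3. If discharge is meant, label the SAE window inclusion to discharge. Do the same for patients already past day 30 who were not asked these questions. At the last reported count 126 of 200 patients had been recruited, so at that date the added questions could still reach the remaining 74.
4. In either case show SAEs per arm with observed patient-days, and separate in-hospital from post-discharge events.

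The cost is a few questions in an existing call and one denominator column. Days from inclusion to discharge are already recorded as a procedural variable, so the in-hospital denominator (capped at 30 days) needs no new data. The downside is that events after discharge would be reported by the patient or institution and be less well documented, which is a reason to list them separately.
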